#### Phase 1: data collection and analysis

The evaluation will employ a multiple case study approach [81], with the participating workplaces as the units of analysis. The evaluation of the cases will be guided by the conceptual framework for knowledge transfer, dissemination, and utilization for sun safety in outdoor workplaces (Fig. 1) to capture changes in programs, policies, and procedures. Workplace evaluations will occur at three points in time. The baseline assessment will focus on understanding the unique characteristics of each workplace, their occupational health and safety management system, and their current sun safety policy and practices. The second evaluation will be conducted after the first summer (mid-point of the study). The third workplace evaluation will be conducted 18 months after the study’s start date. Finally, a cross-case evaluation matrix will be used to determine generalizable patterns and themes.

Data collection will use mixed methods involving multiple sources of information including semi-structured key informant interviews and focus groups with workers, management, and the occupational health and safety specialist to determine the current occupational health and safety policies and procedure, readiness to change, organizational culture, and barriers/facilitators to sun safety programming (for example, see Fig. 11 information and consent form). The focus groups with employees will explore barriers and facilitators from the perspective of the different workplace parties—workers, supervisors, managers, and occupational health and safety specialists—and a survey will address individual knowledge, attitudes, and behaviors toward sun safety in the workplace. Site observations will record the use of sun safety practices, and a UV dosimetry assessment will measure UV exposure of the employees in the second summer of engagement.

**Fig. 11 Fig11:**
[figure not shown]
Sun Safety at Work consent form for interview with occupational health and safety lead

The data collection at baseline and mid-point will be conducted by the Sun Safety Advisors. The data collection at the final time point will occur by an independent researcher. This approach is being undertaken because the involvement of the Sun Safety Advisors in the baseline and mid-point evaluations is considered to be part of their relationship-building and knowledge translation activities with the workplaces.

The conceptual framework (Fig. 1) will guide the interpretation and analysis of the qualitative findings for each of the cases. The qualitative data will be coded and organized by the dimensions of the conceptual framework, including the details of the workplace context, the characteristics of the knowledge transfer intervention, the knowledge exchange, and the workplace’s knowledge utilization, including indicators of conceptual use, effort to use, procedural use, and structural use. Short-term and medium-term outcomes will be noted. Key issues and emergent themes will be identified. The quantitative data (surveys) will be analyzed with SPSS or SAS and will allow for comparisons across the three points in time and allow for cross-case comparisons.

A cross-case analysis of the evaluation data from the 13 workplaces will be conducted in order to determine differences in the interventions, the context, and the barriers and facilitators that led to changes in policies, procedures, and practices on sun and heat protection. The cases will be compared by provincial jurisdiction (12 of the workplaces are in 3 provinces and fall under provincial legislation, and one workplace is federally organized). Although all the provinces have a version of the “General Duty Clause” to protect workers from unsafe work, the different legislative frameworks do lead to different barriers and facilitators. The companies will also be compared by industry (line workers or municipality); size of workplace (small, medium, or large); readiness to change (as determined by the sun conceptual framework); the interventions they chose (for example, the intensity of the interaction with the Sun Safety Advisors, training, and investment in personal protective equipment); the barriers and facilitators that emerged during the implementation; and the changes in programs, policies, and practices that took place over time as noted by the three-points-in-time evaluation. It will facilitate a better understanding of the ways in which the different workplace parties responded to the intervention, and the barriers and facilitators to the adoption of sun and heat protective measures, and enable the team to refine the suite of resources for a broad outreach to companies across Canada.

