**Fig. 10 Fig10:**
[figure not shown]
Sun Safety at Work sun safety advisor training meeting

The Sun Safety Advisors will interact with one to four workplaces each depending upon geographical convenience. To initiate their relationship with the workplaces, they will meet with their worksites together with the project partner who made the initial contact to reassure the workplace of the level of support offered by the project team. They will engage with the participating worksites (including regular face-to-face contact) with management and workers, and will identify an internal “workplace champion” with whom to work closely. The workplace champion will be the workplace liaison and local project sponsor. The importance of the champion role has also been well explored as a means to ensure sustainability [80]. In previous projects of this type, the workplace occupational health and safety professional has often fulfilled this “workplace champion” role because of their involvement in occupational health and safety projects.

The project officers will collect the evaluation data at base-line before and after the first summer. This includes worker surveys and a face-to-face interview with the health and safety champion and managers. The interview information will focus on assessing the workplace’s organizational readiness for change; the worker surveys will evaluate workers’ awareness and knowledge of heat and sun protective behavior and practices, and when compared with the second evaluation, we will have metrics of change due to the intervention.

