#### The Sun Safety at Work implementation

The Sun Safety Advisors will help the companies develop their programs and policies (Sun Safety Action Plans), based upon the findings of the base-line surveys and interviews. The action plan will be tailored to suit each workplace and will be embedded within the companies’ occupational health and safety risk assessment and control framework and risk management systems. It will describe the evaluation process of the project and will specify proposed sun safety activities, the timeline for implementation, who is responsible, and how these activities fit into the legal obligation to create a safe workplace. The action plan will be for 3 years and will extend beyond the project’s funding and direct involvement to ensure sustainability of the initiatives in the workplaces.

The action plan will take into account the financial and organization capacity of the workplace to implement the activities, and depending upon where a workplace is on their sun safety “journey,” will include a phased approach to the implementation of the selected activities. The ability of the workplace to sustain their sun safety program (after the study is over) and their overall stated level of change commitment and sense of efficacy will be a key determinant for the selection of activities and the development of the action plan.

During the first summer, the Sun Safety Advisors will lead the educational initiatives by delivering toolbox talks, showing videos, attending and contributing to joint occupational health and safety committees, giving health and safety meeting presentations regarding sun safety topics, promoting and exhibiting sun safe behavior including the wearing of appropriate PPE, and generally providing current and accurate educational advice to be disseminated to the workforce. They will also advise on how best to implement programs and sun safety change initiatives the employer chooses to undertake and help implement any of the initiatives from a suite of resources proposed by the study.

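### Program deliverers collect the first two waves and an independent researcher the third, so collector is fully confounded with the final wave and the mid-point data are gathered by the deliverers on their own work

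*Protocol article*

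**What the plan says.** Under Phase 1: data collection and analysis, the protocol article assigns the collectors by wave: "The data collection at baseline and mid-point will be conducted by the Sun Safety Advisors". For the last wave, "The data collection at the final time point will occur by an independent researcher". The reason given for the split is that the Advisors' part in the first two evaluations "is considered to be part of their relationship-building and knowledge translation activities with the workplaces".

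The section on recruitment of Sun Safety Advisors, where the Advisors are also called project officers, agrees: "The project officers will collect the evaluation data at base-line before and after the first summer". It adds the instruments: "This includes worker surveys and a face-to-face interview with the health and safety champion and managers". It goes on to say that comparing the worker surveys with the second evaluation will measure change caused by the intervention.

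The same people deliver the program. Under The Sun Safety at Work implementation: "The Sun Safety Advisors will help the companies develop their programs and policies (Sun Safety Action Plans", and "During the first summer, the Sun Safety Advisors will lead the educational initiatives by delivering toolbox talks".

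The section on guiding frameworks makes workplace-level change in policies, procedures and practices the major outcome. The analysis section plans survey comparisons over the three waves and uses change over time in the cross-case comparison.

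**The concern.** Two separate things happen to the measurement while the program runs.

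- **The collector's role changes between baseline and mid-point.** At baseline the Advisor is new to the site. At mid-point the Advisor has spent a summer training the workers and supporting the action plan, and then asks about the result.
- **The collector changes between mid-point and final.** Someone with no part in delivery takes over.

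The first bears on the contrast that the article reads causally. The second bears on whether change lasted, which the study's sustainability aim depends on. If respondents are kinder to their own trainer, a sustained effect could look like a relapse, and no effect could look like a gain followed by a loss. The cross-case analysis also compares sites by how intensively they dealt with their Advisor. If closer contact makes mid-point answers more favourable, an apparent dose-response could arise from reporting alone.

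**Working it through.** **Inputs.** 13 workplaces, three waves and the collectors as set out above, all from the protocol article. It gives no number of workers per wave, no expected change and no figure for collector influence on this point. There is thus no planned figure to reproduce, and the check is one of identifiability.

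**Step 1: can collector and time be separated?** Take a model with 13 workplace effects, indicators for waves 2 and 3, and an indicator for the independent researcher. It has 13 × 3 = 39 rows and 13 + 2 + 1 = 16 columns. Its rank is 15, because the collector column equals the wave 3 column in every workplace. The two effects cannot be estimated separately.

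**Step 2: which contrasts are exposed?** Let a1 and a2 be the recorded-minus-true level when the Advisor collects at waves 1 and 2, and r the same for the independent researcher at wave 3. The bias in each contrast is:

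- wave 2 − wave 1: a2 − a1
- wave 3 − wave 2: r − a2
- wave 3 − wave 1: r − a1

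*Case A, the switch alone* (a1 = a2, with b = r − a1). The shifts are 0, b and b. A fitted linear trend over the whole span shifts by the wave 3 weight times the span. With equal spacing (0, 1, 2) this is 1/2 × 2 = 1.00b. With waves at 0, 6 and 18 months (assumed), the mean is 8, the deviations are −8, −2 and 10, and their squares sum to 168, so the shift is 10/168 × 18 = 1.07b.

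*Case B, favourable reporting to the trainer at mid-point only* (a1 = r = 0, a2 = f). The shifts are +f, −f and 0. The equally spaced trend is unaffected; at 0, 6 and 18 months it shifts by −2/168 × 18 × f = −0.21f.

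The two cases affect different contrasts, and the three waves cannot show which case applies.

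**Step 3: an illustration for survey percentages, on assumptions only.** Assume 30 workers per site per wave (13 × 30 = 390), a proportion of 0.5 and an intracluster correlation of 0.05. The standard error of a difference between two waves is

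- √(2 × 0.25 × (1 + 29 × 0.05)/390) = 0.056 if site effects are uncorrelated between waves;
- √(2 × 0.25 × 0.95/390) = 0.035 if site effects are fully stable.

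Under case B, f = 5 points would be 0.9–1.4 standard errors, 10 points 1.8–2.9, and 15 points 2.7–4.3. This shows only that a moderate reporting effect could match sampling error in the wave 1–2 and 2–3 contrasts. It says nothing about the workplace-level policy outcomes.

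**Step 4: which data are exposed?**

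- Interviews and focus groups: most, since the answers are given to the collector.
- Site observations: also high. "Site observations will record the use of sun safety practices", which depends on the observer. The article does not say at which waves they are made, so an Advisor as observer at mid-point is read from the general sentence on collection.
- Worker surveys: less if self-completed; the mode is not stated.
- Written policies: less, since the document exists whoever asks for it.
- UV dosimetry: planned only in the second summer, so it gives no trend over waves and cannot serve as an objective check.

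**The case against.** The split is deliberate and its reason is given. The design is presented as a multiple case study meant chiefly to explain implementation, and the summary concedes the limits of a before-after comparison without controls. Independent collection at the final wave is a strength: under case B it leaves the baseline-to-final contrast clean. Survey mode and coding staff are details an article may leave to the full protocol, so self-completed surveys may already be planned.

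Much of this stands, and it rules out stronger readings. A reader might infer that the trend over waves is biased, or that it will show false decay. The documents do not support that: they give no size or direction, and which contrasts shift depends on the mechanism. A reader might also infer that the Advisors write the policies they later count. The article says only that they help the companies develop them, and that the employer chooses which initiatives to undertake.

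Three things remain. The stated reason explains why Advisors should be present, but it does not make the waves comparable. The conceded limitation does not mention the collector. And the article states a causal reading of the baseline to mid-point change, which goes beyond what deliverer-collected data can carry.

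**Conclusion.** The concern holds in a limited form. Collector is fully confounded with the final wave in all 13 workplaces, so contrasts with that wave are open to a collector effect that no analysis of these data can separate from time. The baseline to mid-point contrast is not touched by the switch, but it is open to favourable reporting to the trainer, and attributing it to the intervention is not justified.

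The size is unknown. A constant collector difference b enters both final-wave contrasts in full, and b is zero only if the collector has no influence on answers or ratings. The percentages above rest wholly on assumed inputs. There is also an overlap between delivery and outcome: an action plan produced with Advisor support is part of the program at each site and should not by itself count as policy change. This should be fixed, but it does not undermine the study as a whole.

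**What to change.** Keep the Advisors in the interviews, so that the relationship-building purpose is preserved, and make four changes.

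1. Have worker surveys self-completed at all three waves and returned directly to the coordinating team, by sealed envelope or link, not through the Advisor.
2. Have the independent researcher already planned for the final wave score policy, procedure and practice outcomes for all three waves on one rubric, from employer documents, transcripts and observation sheets. Mask the wave only where feasible: dates on documents and mentions of the program in transcripts will often reveal it.
3. Log the Advisor-supported action plan as delivery. Count as outcome only policies and procedures that the employer has formally adopted and put into use.
4. State the remaining change of collector as a limitation, read final-wave contrasts with it, and drop the wording that attributes the baseline to mid-point change to the intervention.

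No new staff or visits are needed. The cost is scoring time for 13 × 3 = 39 site-waves of material, plus survey returns. Rescoring puts the waves on one scale but does not remove influence already in the answers, which is why the fourth change is needed as well. Collection by both parties in parallel at one wave would allow the collector difference at that wave to be estimated, but it would add visits. The trial status section reports recruitment, hiring and training but no data collection, so on this text the changes could still be made.

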#### Phase 2: data collection and analysis

The aim of phase 2 is to develop the sun safety program for use by a national audience by developing relationships with policy, practice, and regulatory agencies. This initiative will be based upon the learnings identified from working with the specific workplaces in phase 1. Learnings will relate to the effectiveness of specific sun safety initiatives, with particular reference to the characteristics of the individual workplaces and identified sectors. In this phase of the study, we will use social marketing principles and be guided by a dissemination and knowledge transfer conceptual framework (Fig. 3) to promote the use and adoption of the resources and strategies. The project partners will interact intensively with policy advocates, industry decision-makers, and the workplaces from phase I to engage them as knowledge brokers to disseminate the findings. This interaction has already begun in the three provinces with identifying which organizations, associations, and policymakers should be targeted and kept informed as the study progresses. A knowledge broker, who was hired at the beginning, will lead this initiative.

We will develop a website with materials for workplaces on sun and heat protection. The program will be hosted on an interactive website that will enable workplaces throughout the country to implement effective sun safety policy and practice on their own. Company OHS leads will be able to download targeted material depending upon their current “stage of readiness,” using the organizational readiness for change “Sun” model as a guide (Fig. 5). As such, the website will enable workplaces to adapt the resources to their own needs and characteristics and to their current stage of policy and practice. The resources will help guide workplaces in planning and implementing sun safety practices in a progressive manner.

In addition to these customizable resources, more general resources to support and emphasize the importance of occupational sun safety will be developed and made available on the website. These will include summary statements and resources for use by workers, management, and occupational health and safety practitioners, policy briefing notes for regulators on particular outcomes of the research (from phase I), a series of short videos of worker experiences with skin cancer and heat stress, and videos that record workplaces’ experiences implementing sun safety programs.

As the key outcome of the project is to influence policy and practice, a knowledge translation dissemination strategy for broad reach (i.e., to all Canadian workplaces and workers) will be developed progressively while the project is being implemented and based upon the phase 2 logic model (see Fig. 4). This strategy will allow for the immediate and sustainable exchange and translation of the learnings of the project for a broader workplace audience.

The tools and resources developed for broad reach will be disseminated by the project’s partners and their network of industry decision-makers in a deliberate and coordinated effort to influence policy and practice. This will include using the project’s database of over 10,000 email addresses of OHS practitioners from across Canada, from multiple sectors, as a way of making direct contact to advise them of the tools/resources available, posting information about the tools/resources through social media, hosting workshops in each of the project locations, and having a dedicated website that contains the tools and resources developed for phase 2. A series of regional workshops on the project findings and how to use the developed resources will also be hosted for safety professionals and others from industry and government.

The use and “traffic flow” through the dedicated website will be monitored to gain an understanding of the reach and popularity of the different tools and resources. A survey on the website will allow visitors to provide feedback on the effectiveness of the tools and resources. In addition, a survey of policy and practice stakeholders will be conducted on the usefulness and effectiveness of the tools and resources and on how they have been used and how they have influenced policy and practice.

### Ethics approval

The Community Research Ethics Board (APP7/18/14) has approved this study protocol, and the Research Ethics Board at Ryerson University has deemed that “Based on the information provided the project falls within Article 2.5 of the federal guidelines governing research ethics and so does not require Research Ethics Board review” (REB 2014-263). Participation agreements were signed between the participating project partner agencies. Letters of information will be given out, and written consent will be received by all those engaged in the UV dosimetry study, the interviews, focus groups, and surveys. The letter of information highlights the objective of the study, the composition of the research team, who is eligible to participate, the benefits of being involved in the study, that participation is voluntary, and that all the data collected will remain confidential and accessible only to the research team. It also states that the team expects to finish this study in 2 years’ time (fall of 2016), that we will summarize the study findings and share them with the participating workplaces, and that the results will be put on the project website and the website of the Occupational Cancer Research Centre: http://www.occupationalcancer.ca. We also make the commitment to share our results on posters, at presentations, in newsletters, and in research publications.

### Trial status

Workplaces in the four provinces have been recruited, and a project coordinator, the Sun Safety Advisors, and a project knowledge broker have all been hired. The suite of resources has been completed, and the initial training for the advisors has been completed. The branding of Sun Safety at Work and the creation of the website is underway. Representatives from the partner agencies from the four provinces have met three times in person and continue to have monthly teleconferences. Subgroups have been working on the suite of resources, the hiring process, the creation of the training sessions, and the recruitment of workplaces.

